More than 1 unit of the same drug for the same time prescribed	Scanned once, then the number of tablets is manually adjusted	Every drug unit is scanned	Scanned once, then the number of tablets is manually adjusted	Scanned once; a pop-up appears asking for the other tablets to be scanned
Patient away or sleeping	Prescribed medication is placed at the patients’ bedside, registered as given, and checked at 2:00 AM	Medication not given and not registered; noted in memo field	Medication not given and not registered; noted in memo field	Not described in the instructions
One-half or one-quarter of a tablet prescribed	Tablet scanned, plus code “half” or “quarter” scanned on computer	Not described in the instructions	Tablet scanned, plus noted by nurse in memo field on the screen	Not described in the instructions
Instructions on screen for nurse from pharmacy or prescriber	On-screen memo field included (medication data level)	On-screen memo field included (patient data level)	On-screen memo field included (medication data level)	On-screen memo field included (medication data level)

We will collect the following potential risk factors for workarounds using a structured data collection form (Multimedia Appendix 1): nurses’ characteristics (experienced, trained, or student nurse; nurses’ satisfaction with BCMA), workload characteristics (number of nurses on the ward, number of patients served by that ward, number of medicines per round per patient, number of medicines for all patients per round per ward), BCMA system characteristics (time after implementation of BCMA system on that ward, bar code on medication unit dose), medication characteristics (Anatomical Therapeutic Chemical Classification System [ATC] code of the medication, drug administration route), and general characteristics (hospital type, ward type, time of ward round, patient age and sex). We will ask the supervisor of the ward for data on the nurses’ education and experience. We will extract the number of patients on the ward, the medication and ATC code, and the number of drugs to administer to each individual patient during the specific administration rounds from the CPOE system. We will ask the supervising hospital pharmacist for the other risk factors.

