### Sample Size Calculation

Prior studies [14,44-46] on the effect of BCMA show a substantial reduction (about 30%) of errors after the implementation of BCMA (from 14.4%, or 4743 errors in 32,972 observations, to 9.9%, or 2651 errors in 26,892 observations). The error rate of about 10% is a mix of all resulting errors, including those caused by workarounds. The purpose of our sample size calculation is to estimate the number of observations needed to reject the null hypothesis with a power of 90%. We performed a pilot study in 4 Dutch hospitals that were partially using BCMA (these hospitals did not participate in our final research) and found MAE rates, including time window errors caused by nurses and based on workarounds, fluctuating from 2% to 20% (2%, 4%, 5%, and 20%). We assume in our sample size calculation that 8% of medication administrations per patient per nurse result in a workaround. We also assume that the MAE rate associated with a workaround is 2-fold compared with the situation without a workaround; that gives us a relative risk of 2. With alpha of .05 and a power of 0.9, we need to observe 1500 individual medication administrations to patients per hospital to reject the null hypothesis.

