### Statistical Analysis

Data will be analyzed using IBM SPSS Statistics version 22 (IBM Corporation). We will analyze the potential association between workarounds and the occurrence of MAEs using univariate multilevel logistic regression, with the proportion of medication administrations with 1 or more errors as the dependent variable and the occurrence of workarounds as the independent variable. The nurse and the patient will be the levels in the multilevel analysis. We will analyze the occurrence of workarounds as a categorical variable, with the following categories: no workarounds (reference category), 1 workaround, 2 workarounds, and 3 or more workarounds. We will adjust for potential confounders by using multivariate multilevel logistic regression. The parameters in the multivariate multilevel logistic regression model will be hospital, ward type, day of the week, time schedule of medication administration rounds, ATC code, the number of drugs per patient per round, and the route of administration. We will report the adjusted odds ratio and 95% confidence interval. For the frequency and type of workarounds and MAEs, we will use descriptive statistics. Univariate and multivariate logistic regression will determine the association of the risk factors with the workarounds.

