### Strengths and Limitations

The strength of the Dutch BCMA study is that it will provide quantitative information about workarounds and their possible association with MAEs, as one of the first studies worldwide, to our knowledge. Other strengths are the multicenter design, which enhances its generalizability, and the robust method of data collection by disguised observation.

There are some limitations and considerations, however. An important limitation, in general, is that the use of BCMA cannot prevent all MAEs. For example, BCMA systems will have no influence on the preparation of intravenous and nonintravenous medication. So, although this study will contribute to patient safety, further studies into other ways of preventing MAEs will remain necessary.

Although disguised observation is the best method for data collection in MAE studies, some limitations are associated with this technique. Despite thorough training of the observers, bias may still occur. To overcome observation bias, we considered the use of the work observation method by activity timing [34,48]. This elegant paperless method is used for time- and activity-based observations and is less suitable for observing workarounds and MAEs.

The observations may influence the nurse but, from the literature, we know that this effect (known as Hawthorne effect) [49,50] is small. The observer may also become tired and thus less accurate. How to train observers is not well documented in the literature. Patterson et al [19] performed an observational study in acute and long-term care wards using observers trained in ethnographic observations in complex settings. Other researchers trained nurse students as observers [51]. We will use all possible means, as well as the best possible literature base, to train the students.

We will try to reduce confounding by applying multivariate regression analyses (eg, hospital type, type of ward). However, in this type of observational study design, residual confounding may always remain [52].

Last but not least, we plan to conduct our research on internal medicine and surgical hospital wards. Although these nursing wards cover a broad range of patient categories, our findings cannot be generalized to all patient categories.

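### The planned workaround odds ratio mixes within-nurse and within-patient associations with between-cluster ones; a within/between breakdown should be reported beside it

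*Protocol article*

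**What the plan says.** Under Statistical Analysis the exposure is measured per administration, in four categories: "no workarounds (reference category), 1 workaround, 2 workarounds, and 3 or more workarounds". On clustering: "The nurse and the patient will be the levels in the multilevel analysis". Besides the administration route, the adjusted model contains "hospital, ward type, day of the week, time schedule of medication administration rounds, ATC code, the number of drugs per patient per round". On reporting: "We will report the adjusted odds ratio and 95% confidence interval".

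That list has no nurse variable, no patient age or sex and no nurse-average or patient-average workaround term, and no within-nurse or conditional analysis is named. Outcome Measures does list "nurses’ characteristics (experienced, trained, or student nurse; nurses’ satisfaction with BCMA" among the data collected, but as possible risk factors for workarounds. Strengths and Limitations concedes in general terms that "in this type of observational study design, residual confounding may always remain".

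**The concern.** A random intercept for nurse or patient is assumed to be independent of how often that nurse or patient has a workaround. When it is not, the single coefficient is a weighted mix of two associations. The within-cluster part compares administrations by the same nurse to the same patient. The between-cluster part compares different nurses and patients, and carries every unmeasured difference between them.

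The Discussion gives a reason to doubt independence. It attributes many technology-related errors to poor training, poor grasp of the system or deficient equipment, and says such factors may prompt workarounds. That is a possible common cause, partly at nurse level. Data Collection asks observers to cover as many nurses as they can, which favours few administrations per nurse, the situation in which the mixing is worst.

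At stake is how the result is used. The abstract's conclusion is that an established association can serve to lower the error rate. Whether to act on the bypassing itself, or on particular nurses, wards or patient groups, depends on which part of the association is present. The repeated administrations already collected can help to separate the two.

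**Working it through.** **The plan's own figures.** None bears directly on this point. The sample-size statement ("With alpha of .05 and a power of 0.9, we need to observe 1500 individual medication administrations to patients per hospital") supplies only the scale: 4 × 1500 = 6000 administrations. It also assumes that "8% of medication administrations per patient per nurse result in a workaround", and a relative risk of 2.

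**Models compared**, for an administration by nurse *j* to patient *k*, with W = 1 if there is a workaround:
- Planned type: logit P(MAE) = α + βW + u_j + v_k, with u and v independent of W.
- With cluster means: logit P(MAE) = α + β_w W + δ_n W̄_j + δ_p W̄_k + u_j + v_k. Here β_w is the within-cluster effect. Each δ is the amount by which the between-cluster association differs from it.

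**Assumptions.** The true odds ratio is 1. Numbers of clusters, standard deviations (SDs) of cluster effects and correlations are assumed, because the article gives none. W is binary, and the plan's adjusters are not simulated, so each correlation stands for what remains after adjustment.

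**One cluster level** (6000 administrations, about 8.5% workarounds, about 11% errors, cluster SD 1.0 for workaround and 0.8 for error, 120 runs per row):

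| Clusters × size | Correlation | Planned type: OR, rejection | With cluster mean: OR, rejection | SE of log OR |
|---|---|---|---|---|
| 600 × 10 | 0.5 | 1.27, 33% | 1.00, 6% | 0.146 → 0.154 |
| 600 × 10 | 0.3 | 1.14, 13% | 0.99, 4% | 0.151 → 0.161 |
| 150 × 40 | 0.5 | 1.09, 8% | 0.98, 4% | 0.148 → 0.151 |

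The SE ratios are 0.154/0.146 = 1.05, 0.161/0.151 = 1.07 and 0.151/0.148 = 1.02. Repeats of the two correlation-0.5 rows gave 1.24 and 1.25 for 600 × 10, and 1.11 and 1.12 for 150 × 40.

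**Nurse level only, by cluster size** (8% workarounds, 30 runs per cell). OR from the planned type of model at correlation 0.5 / 0.9:
- 100 administrations per nurse: 1.10 / 1.09
- 30 per nurse: 1.18 / 1.29
- 10 per nurse: 1.30 / 1.64

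Adding the nurse mean gave 0.97 to 1.04. With no correlation both models gave 0.95 to 1.03.

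**Nurse and patient crossed** (200 nurses, 600 patients, about 7% workarounds, 24 runs per cell):

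| Correlation: nurse, patient | Planned type: OR, rejection | With both means: OR, rejection |
|---|---|---|
| 0, 0 | 0.96, 0% | 0.97, 0% |
| 0.5, 0.5 | 1.22, 21% | 0.94, 4% |
| 0.8, 0 | 1.15, 17% | 0.94, 0% |
| 0.8, 0.8 | 1.48, 54% | 1.00, 4% |

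**Strongly clustered workarounds** (600 × 10). With workaround SD 3 and no correlation the SE rose from 0.183 to 0.228 (ratio 1.25). With SD 5 it rose from 0.180 to 0.269 (ratio 1.49). With SD 3 and correlation 0.5 the planned type of model gave an OR of about 1.65.

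**Precision of these figures.** An 8% rejection rate in 120 runs has a Monte Carlo standard error of √(0.08 × 0.92/120) = 2.5 points, so it is not clearly above 5%. For 54% in 24 runs it is √(0.54 × 0.46/24) = 10 points.

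**Scale against the target effect.** The error rate behind the sample size is not stated. If it is 10% overall, the rate without a workaround is 0.10/(0.92 + 2 × 0.08) = 0.0926 and with one 0.1852. The target OR is then (0.1852/0.8148)/(0.0926/0.9074) = 2.23, with log 0.80. Over the pilot range of 2% to 20% it runs from 2.04 to 2.59. At 10%, a spurious OR of 1.10 is ln 1.10/0.80 = 12% of the target on the log scale, and 1.25 is ln 1.25/0.80 = 28%.

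**The case against.** **The plan does not say that nurses prone to workarounds are prone to errors.** A reader might infer from the risk-factor list that the plan itself assumes a violated model. The list does not support that: it concerns workarounds only, and bias needs a link to errors as well. The Discussion comes closer, but it speaks generally and does not say how large the shared part is.

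**Random intercepts are inferred, and the article is condensed.** Both are true. But the exposure, the levels and the list of adjusters are stated, so this is a comment on a stated choice and does not ask for missing detail.

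**The aim is association, and residual confounding is disclosed.** This stands as far as the odds ratio is described as an association. It does not cover the step to action in the abstract, and the disclosure does not mention that confounding constant within a nurse or patient can largely be addressed with the data in hand.

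**The size is modest where the story is most tempting.** That careless nurses would manufacture the result is not supported: nurse-like clusters of 40 to 100 gave about 1.1. The larger patient-like figure arises where number of drugs, drug class and route are already adjusted for. Neither figure would produce a relative risk of 2.

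**The within-cluster estimate has costs.** Patients are generally selected once per round (Table 1), so a missing wristband can affect all of a patient's doses in that round and vary little within the patient. The within-cluster estimate then discounts relevant between-patient evidence and loses precision. This stands, and is why it should accompany the planned estimate and not replace it.

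**Conclusion.** The point holds in a limited form. The planned odds ratio is a legitimate measure of association, but alone it cannot distinguish an effect of bypassing the check from a tendency of the same nurses or patients to have both workarounds and errors. If the true within-cluster odds ratio is 1 and the remaining correlation is 0.5, the spurious value is about 1.1 in large nurse-like clusters and about 1.25 in small patient-like ones. It rises to about 1.65 if workarounds cluster strongly within small clusters, and is absent if there is no correlation. All of these sizes rest on assumed cluster sizes, SDs and correlations. The documents do not show that the bias is present, and they do not support calling the planned analysis invalid.

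**What to change.** Keep the planned adjusted odds ratio. Beside it, as a pre-specified companion analysis, fit the same model with two added covariates: each nurse's and each patient's proportion of observed administrations with a workaround. Report the within-cluster and between-cluster estimates together. Base any statement that workarounds themselves lead to errors on the within-cluster estimate. Because the Results section says analysis is under way, record when this analysis was specified relative to sight of the error results.

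The simulations used a binary exposure. With three workaround contrasts, one any-workaround proportion per level is an approximation, and this should be stated.

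No new data are needed. The cost is a wider interval for the within-cluster estimate: about 2–7% on the standard error with modest clustering of workarounds, and 25% or more with strong clustering. The analysis does not remove confounding that varies by dose or by round, and the report should say so.

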### Setting

All included hospitals have implemented CPOE [10] and BCMA systems. They use a variety of software packages, both for the CPOE and for the BCMA systems. As a consequence, procedures for prescribing and medication administration differ between hospitals. Table 1 summarizes the main characteristics. Medication administration procedures within a hospital vary slightly between wards because of differences in patient groups or tasks (eg, in some hospitals, short stay surgical patients do not wear wristbands, but these are attached to the medication cart).

The included hospitals use bar code-labeled unit dose systems to distribute medication to inpatients. In the pharmacy departments, pharmacy technicians dispense bar coded medication for individual patients into trays labeled with the patient’s name and bar code. Trays are placed in medication carts in which they are then delivered to the wards once a day (or more frequently). Wards do not have ward-based medication stock (except for emergency medication). One of the selected hospitals uses so-called bedside assortment picking carts [29]. A cart contains all the medication commonly used on the ward. With this system, nurses select the medication for administration during the medication administration rounds.

In general, there are 4 scheduled medication administration rounds in the participating hospitals: 6-10 AM, 10-2 PM, 6-8 PM, and 8-10 PM. Medications are administered by 1 nurse. Nurse trainees are supervised by registered nurses. In the participating hospitals, there are approximately 10-20 inpatients admitted on a ward served by a registered nurse and a nurse trainee. A large ward is split into smaller units each serving 10-20 inpatients, each aided by a registered nurse and a nurse trainee.

During a drug administration round, nurses select the prescribed medication for each inpatient from the prefilled trays or from the bedside assortment picking carts. In addition to the cart, nurses also take along the computer on wheels or the workstation on wheels to access the CPOE system during the drug administration round.

Inpatients do not use their own (out-of-hospital prescribed) drugs.

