### Participants

The study will enroll patients admitted to the internal medicine and surgical wards of 4 Dutch hospitals in which a BCMA system is used to administer medication. To be eligible to participate in this study, a participant must meet the following criteria: be a hospitalized patient and receive medication on those nursing wards that are participating in this study. We will exclude patients younger than 18 years.

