### Data Collection

We will use disguised observation [30-34] to collect data. A total of 3 trained observers (undergraduate students, writing their master’s thesis) from the School of Pharmacy, University of Groningen and Utrecht University, the Netherlands, will observe the nurses while they give drugs to inpatients. To prevent nurses adjusting their behavior in the BCMA process while under observation, the observer will be introduced as being on the ward to monitor the performance of the medication distribution system on that ward. The observer will take part in several planned medication administration rounds on that ward and also observe unscheduled medication administrations. The observer will randomly pick a medication administration round with a minimum of 3 rounds every day and a weekly minimum of 18 rounds. During the different rounds, the observer will observe as many different nurses as possible. To prepare for the observation, the observer will study the standard operating procedures or the applicable drug administration procedures of the specific ward and the agreements on the BCMA process of that ward. In practice, the observer will accompany the nurse who administers the medication using the BCMA system and observe the administration of each dose of medication to the patient. The observer will record the nurses’ actions of giving drugs to the patients (according to the forms in Multimedia Appendix 1,Multimedia Appendix 2, and Multimedia Appendix 3). After each observed medication administration round, we will collect a (printed) computer output of the medication for that specific patient, day, and round from the hospital’s electronic patient records. Consequently, we will compare observation records with the prescribed medication on this computer output and with available standard operating procedures of the BCMA process for that specific ward, to identify workarounds and MAEs. We designed an Access database in which we will record the observation data and which we will link to each patient’s prescription and medication data.

If the observer becomes aware of a potentially serious error, the observer will intervene for ethical reasons, but the data will be included in the study.

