### Definitions and Classification

Workarounds are defined as “informal temporary practices for handling exceptions to normal workflow” for that specific ward and are operationalized as deviations from the available protocols [24]. Figure 1 depicts the BCMA workflow and the potential risk factors for workarounds in the BCMA process. We will classify workarounds using a self-developed classification system (Table 2) derived from the system of Koppel et al [26]. Workarounds can be related to patient identification, the scanning process, the alert signals, and other procedures, or can be work related. Allan and Barker [41] defined MAEs as “the administration of a dose of medication that deviates from the prescription as written (or ordered by CPOE) on the patient medication chart, or from standard hospital policy and procedures.” We will compare drug administrations with the doctor’s prescriptions as noted in the CPOE system in the pharmacy database. We will exclude intravenous and nonintravenous preparation errors because these errors are not preventable by BCMA and are thus unlikely to be influenced by workarounds in the BCMA process. We will classify the MAEs using the classification of van den Bemt et al [42] (Table 3). We will divide the number of erroneous medication administrations (containing 1 or more errors) by the number of observed drug administrations plus the number of omissions, thus using the concept of opportunities for errors as in other MAE research [43].

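### Ward is neither a covariate nor a level of the MAE model, so ward-level confounding may remain in the adjusted odds ratio

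*Protocol article*

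**What the plan says.** The Statistical Analysis section of the protocol article specifies the adjusted model for the primary association: its parameters "will be hospital, ward type, day of the week", followed by the time schedule of the rounds, ATC code, number of drugs per patient per round and route. On clustering it says: "The nurse and the patient will be the levels in the multilevel analysis". The result to be reported is given as "We will report the adjusted odds ratio and 95% confidence interval".

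Three other sections tie the measurements to the ward:

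- Definitions and Classification defines workarounds as practices "for that specific ward and are operationalized as deviations from the available protocols".
- Data Collection says that observations are compared with the prescription output and "with available standard operating procedures of the BCMA process for that specific ward, to identify workarounds and MAEs". The ward's procedures therefore serve for both exposure and outcome.
- Setting says: "Medication administration procedures within a hospital vary slightly between wards because of differences in patient groups or tasks". Its example is short-stay surgical patients in some hospitals, whose wristbands are kept on the medication cart.

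The Participants section describes the sites only as "internal medicine and surgical wards of 4 Dutch hospitals". Neither the number of wards nor any ward-level rate of workarounds or MAEs is given.

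**The concern.** The comparison of interest is between doses with and without a workaround given under the same procedures. For that, whatever varies between wards and affects both variables has to be held constant. Ward type does this only if wards of one type in one hospital are interchangeable.

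There are three reasons to doubt that they are.

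- **Exposure.** The same act can be a deviation on one ward and normal procedure on another. Table 2 gives scanning a loose wristband as an example of a workaround, while the Setting section describes patients for whom a wristband off the patient is the arrangement.
- **Outcome.** The MAE definition includes departures from policy and procedures, so the same ward documents can also influence the MAE rate.
- **Other ward features.** Time since BCMA implementation on the ward, number of nurses and number of patients are collected as candidate determinants of workarounds, but are not in the MAE model.

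If such differences act on both variables, the adjusted odds ratio mixes the within-ward contrast with a between-ward contrast, and its confidence interval is centred in the wrong place.

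**Working it through.** The plan gives no figure for this point, so there is none to reproduce; the sample size of 1500 per hospital plays no part in it.

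**Step 1: what the listed terms can separate.** Suppose ward type has two categories and each hospital has one ward of each. There are then 4 × 2 = 8 wards. Additive hospital and ward type use 1 + 3 + 1 = 5 parameters, so 8 − 5 = 3 degrees of freedom of ward differences are unadjusted. With more than one ward per type and hospital, all differences between those wards are unadjusted as well.

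**Step 2: size under assumed ward differences.** From the article: 6000 administrations, 4 hospitals, 8% workarounds, and an overall MAE rate of about 10%. Assumed: 9% MAE without a workaround, 10 nurses per ward, nurse SD 0.3 on the logit scale, W = 1 or 2 wards per type per hospital, ward SD s, and correlation ρ between the two ward effects. The generating model was

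- logit P(workaround) = log(0.08/0.92) + ward effect 1 + nurse effect 1
- logit P(MAE) = log(0.09/0.91) + log(OR) × workaround + ward effect 2 + nurse effect 2

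Each data set was fitted with a nurse random intercept plus (A) hospital and ward type, or (B) ward as a fixed effect. There were 40 replicates per scenario. Workaround was binary, and the patient level and the other covariates were left out.

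| W | s | ρ | True OR 2: A / B | Ratio | True OR 1: A / B | Ratio |
|---|---|---|---|---|---|---|
| 1 | 0.2 | 0.9 | 2.09 / 2.07 | 1.01 | 0.97 / 0.96 | 1.01 |
| 1 | 0.8 | 0.5 | 2.01 / 1.96 | 1.03 | 1.03 / 0.99 | 1.04 |
| 1 | 0.8 | 0.9 | 2.01 / 1.93 | 1.04 | 1.05 / 1.01 | 1.04 |
| 2 | 0.2 | 0.5 | 1.96 / 1.95 | 1.01 | 0.99 / 0.98 | 1.01 |
| 2 | 0.2 | 0.9 | 2.05 / 2.01 | 1.02 | 1.00 / 0.98 | 1.02 |
| 2 | 0.5 | 0.5 | 2.06 / 1.98 | 1.04 | 1.02 / 0.98 | 1.04 |
| 2 | 0.5 | 0.9 | 2.17 / 2.01 | 1.08 | 1.10 / 1.02 | 1.08 |
| 2 | 0.8 | 0.5 | 2.15 / 2.00 | 1.08 | 1.09 / 1.01 | 1.08 |
| 2 | 0.8 | 0.9 | 2.21 / 1.98 | 1.12 | 1.15 / 1.04 | 1.11 |

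Over all scenarios run, model B gave 1.93 to 2.07 for a true OR of 2 and 0.95 to 1.04 for a true OR of 1. That spread also shows the simulation noise.

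**Step 3: what the nurse level does.** In the last scenario (W = 2, s = 0.8, ρ = 0.9, true OR 2), dropping the nurse intercept gave 2.74 against 1.99, a ratio of 1.38. With the intercept the ratio is 1.12. The nurse level absorbs much of the bias, but not all.

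**Step 4: fewer doses per nurse.** A second simulation used a true OR of 1, 3 to 4 wards per hospital, ward SDs of 0.5 to 1.0 (exposure) and 0.5 to 0.7 (outcome), correlation 0.5 to 0.8, and 100 to 120 replicates. With hospital and ward type, the mean OR was 1.04 to 1.09 at about 47 doses per nurse and 1.06 to 1.19 at about 19 (6000/320 = 18.75). With ward fixed effects it was 0.97 to 1.03, with practically unchanged standard errors. Interval coverage was 72% to 95% with ward type and 88% to 95% with ward.

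**Step 5: direction.** At ρ = 0, in runs without the nurse intercept, the ward-type model gave 1.91 to 2.03 for a true OR of 2, so there was no upward bias. The excess comes from the assumed positive correlation. Negative correlations were not simulated; by the same mechanism they would lower the odds ratio.

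**The case against.** A reader might infer that confounding by ward certainly stays in the primary result and inflates it. The documents do not support that.

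- Confounding needs wards within a hospital and type (or hospital-by-type combinations) to differ in both workaround and MAE rates. The article reports neither rates nor a ward count. With one ward per type per hospital the effect is small.
- The Setting section calls the variation slight and attributes it to patient groups or tasks, which ward type may partly capture. The article does not limit ward type to two categories. Its example concerns short-stay surgical patients and does not show that two internal medicine wards differ.
- ATC code, route, number of drugs and round time are already adjusted for, and patient is a level. They address part of any case-mix difference, and the simulations left them out.
- The sign is not fixed. A ward with strict procedures may record more workarounds and yet make fewer errors.
- The 72% coverage belongs to one strong scenario (SDs 1.0 and 0.7, correlation 0.8, 320 nurses). Its Monte Carlo standard error is about √(0.72 × 0.28/100) = 0.045, and ward fixed effects gave 92% there. It does not forecast this study.

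These points all stand, and they limit the claim to a possibility. They do not remove it. A nurse random intercept assumes nurse effects unrelated to exposure and shrinks more when each nurse contributes few doses, which is where observing as many different nurses as possible leads. The caveat on residual confounding under Strengths and Limitations is general, whereas this source is identifiable and can be adjusted for.

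**Conclusion.** The point holds as a possibility, not as a demonstrated bias. The primary model leaves out the unit against whose procedures the exposure, and partly the outcome, is judged. Hospital and ward type stand in for it incompletely, and the nurse level and the listed covariates remove only part of what is left.

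Under assumed positive correlation, the excess in the odds ratio is about 1–2% at ward SD 0.2, about 4% or less with one ward per type per hospital, and about 12–19% only in extreme scenarios. At a planned effect of about 2, even the largest excess in the table (2.21 against 1.98) would not change the qualitative conclusion; near the null it could matter more. All these figures rest on assumed ward counts, ward SDs, correlations and nurse numbers. This is a cheap improvement to the primary analysis, not a flaw that invalidates it.

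**What to change.** In the covariate list of the adjusted MAE model, replace hospital and ward type by ward as a fixed effect. Ward contains both, so no adjustment is lost. If wards are many or sparse, keep hospital and ward type, and add ward as a level together with the ward mean of workaround frequency. A ward random intercept without that mean would not fully remove the confounding. State which unit counts as a ward, since the Setting section says that large wards are split into smaller units; the natural choice is the unit whose procedures served as the reference for the observation.

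The cost is a line of analysis wording and extra parameters on 6000 observations, how many depending on the unstated number of wards. No new data should be needed, because observations are already compared with the procedures of a specific ward. With ward as a fixed effect, hospital and ward type no longer have separate coefficients. They are adjustment terms here and can still be shown in descriptive tables.
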